## Abstract

**Background:**

Individuals who are edentulous have a lower intake of fruit, vegetables, fiber, and protein compared with their dentate counterparts because tooth loss is accompanied by a decrease in ability to chew. Whether or not a combination of prosthetic rehabilitation and simple dietary advice produces improvement in dietary intake among edentulous persons is unclear. We aim to investigate the effect of a simultaneous combination of simple dietary advice delivered by dentists and provision of new complete dentures on dietary intake in edentulous individuals who request new dentures.

**Methods/design:**

Through a double-blinded, parallel, randomized controlled trial in which 70 edentate persons who request new complete dentures will be enrolled, eligible study participants will be randomly allocated to either a dietary intervention group receiving dietary advice or to a control group receiving only advice on the care and maintenance of dentures. Outcome measures include daily intake of nutrients and food items, assessed using a brief self-administered diet history questionnaire; antioxidant capacity, determined using blood and urine samples; nutritional status, assessed with the Mini-Nutritional Assessment-Short Form; oral health-related quality of life, assessed with the Japanese version of the Oral Health Impact Profile-EDENT and the Geriatric Oral Health Assessment Index; subjective chewing ability; masticatory performance, assessed using a color-changeable chewing gum and a gummy jelly; patient self-assessment of dentures; mild cognitive impairment, assessed with the Japanese version of the Montreal Cognitive Assessment; and functional capacity, assessed with the Japan Science and Technology Agency Index of Competence. Outcome measures, except for antioxidant capacity, are to be implemented at three time points: at baseline and at 3 and 6 months following intervention. Antioxidant capacity data are to be collected twice: at baseline and at 3 months following intervention. Differences between the groups at 3 and 6 months and within-group changes are to be compared using the paired *t* test.

**Discussion:**

Simple dietary advice that can be implemented by a dentist would be more practical in clinical practice than tailored dietary counseling. The results of this study will provide beneficial information on dietary intake changes for both edentulous individuals requesting new complete dentures and dentists.

**Trial registration:**

University Hospital Medical Information Network Center Unique Trial Number: UMIN000017879. Registered on 12 June 2015.

## Background

Edentulous individuals consume significantly lower amounts of protein and multiple other nutrients, including fiber, calcium, and some vitamins, because they avoid a number of food types, particularly fresh fruit and raw vegetables and other hard and tough foods, when compared with dentate individuals [1–4]. Several lines of evidence show a relationship between increased intake of some macronutrients and micronutrients and a reduced risk of certain illnesses. Most notably, there is strong evidence that a diet high in fruit and vegetables protects against obesity, diabetes, cardiovascular disease, and some cancers [1, 2]. Poorer food intake by edentulous individuals is therefore likely to lead to ill health. Moreover, inadequate nutrient intake because of tooth loss is associated with weight loss, which is a factor in frailty [5], so edentulous individuals are also at risk of becoming frail.

Previous research has shown that, in many cases, prosthodontic rehabilitation alone, such as complete dentures [1, 6–8], implant overdentures [2, 4, 9–11], and other prosthetic treatments [12–14], for older patients in the absence of tailored dietary counseling is inadequate to attain a significant improvement in nutritional status. Most researchers suggest that dietary counseling is necessary. There has been little research investigating the impact of providing dietary counseling to edentulous individuals wearing complete dentures [1, 3, 15–17]. In a randomized controlled study [16] aimed at edentulous individuals without problems with their current complete dentures or mandibular implant overdentures, tailored dietary counseling benefited both complete dentures wearers and mandibular implant overdenture wearers. Mandibular implant overdenture wearers showed moderately greater dietary improvements when compared with patients wearing conventional dentures. In another randomized controlled study [1] aimed at edentulous individuals who request new dentures, simultaneous tailored dietary counseling delivered by a nutritionist on two occasions and provision of new complete dentures in combination improved fruit and vegetable intake. On the other hand, a combination of use of a denture adhesive and simple dietary advice in the form of government-issued dietary pamphlets issued by dentists produced significant improvement in dietary intake among edentulous individuals wearing current complete dentures for more than one year; there was especially an improvement in the number of portions of fruit and vegetables [3].

There has been no research investigating whether simple dietary advice in pamphlet form combined with provision of new complete dentures improves dietary intake among edentulous individuals who request new dentures. Therefore, we plan to test the null hypothesis that there would be no difference in dietary intake between edentulous individuals provided with simple dietary advice and new complete dentures and edentulous individuals provided with new dentures alone.

## Methods/design

This double-blind, parallel, randomized controlled trial is investigating the effect of a combination of simple dietary advice and provision of new complete dentures on dietary intake in elderly edentulous individuals. The study follows the 2010 Consolidated Standards of Reporting Trials (CONSORT) statement [18]. The study protocol and informed consent documents have been approved by the institutional ethics committee at Tokyo Medical and Dental University (TMDU, registry number 1144). The trial is registered with the University Hospital Medical Information Network (UMIN) Center (UMIN-CTR Clinical Trial, Unique Trial Number: UMIN000017879).

All participants are required to give written informed consent. The study participants are to be randomly allocated either to the dietary intervention group or to the control group. All participants receive complete denture treatments.

### Participants

We are recruiting trial participants as follows:Respondents to flyers in the reception room of the prosthodontics clinic at the University Hospital of Dentistry, TMDURespondents to advertisements in geriatric magazinesRespondents to an announcement on a websitePatients who have received treatment at the undergraduate student treatment clinics at the University Hospital of Dentistry, TMDUNew patients at the University Hospital of Dentistry, TMDU

### Eligibility

Participants will undergo screening to check that they meet the inclusion criteria for the study listed below. Those deemed to be eligible will be asked to give written informed consent for participation in the study before entry into the trial. They will be informed that it is possible to stop participating in the research at any time, and that there will be absolutely no penalty for requesting to stop. The study will be explained to eligible participants by the two outcome assessors (HS and NA), who will also obtain consent directly from the participants. Next, age, gender, family income, education, personal living circumstances, duration of edentulousness, number of previous complete dentures, and degree of ridge resorption are recorded. Gerotranscendence status is then assessed with the Japanese Gerotranscendence Scale Revised (JGS-R) [19, 20], and denture quality by functional assessment of dentures [21, 22] is recorded. In addition, outcome measures are to be assessed at baseline.

#### Inclusion criteria

Each participant included in this study must:Have made a request for new both upper and lower dentures for a dental problemBe able to understand the explanations and instructions given by clinicians or outcome assessorsBe able to understand and respond to the questionnaires used in the studyHave the means to control any recommended dietary change

#### Exclusion criteria

A potential participant will be excluded if he/she has:An infectious diseaseAn orofacial motor disorderA psychiatric disorderA diagnosis of dementiaAny dietary restrictionsNo means to implement dietary change, e.g., a person living in an institution

### Interventions

All patients receive complete denture treatments. The technique used to create a complete denture involves primary and secondary impressions, recording of jaw relationships using occlusal rims, one or two trial insertions, and delivery of the new complete dentures. After delivery, adjustments to the dentures are made until both participant and clinician deem that no further adjustment is necessary. The new complete dentures are made by three dentists with 10–14 years of clinical experience (YK, MK, and MI). They will give complete denture treatments, but will neither deliver dietary advice or advice on care and maintenance of dentures nor assess outcomes. Participants will be randomly assigned to the three dentists.

Participants in the dietary intervention group receive 20 minutes of coordinated dietary advice in the form of an explanation of a pamphlet prepared with reference to the geriatric version of the Japanese Food Guide Spinning Top published by the Japanese Ministry of Agriculture, Forestry and Fisheries. The pamphlet is then given to the participant. If a participant does not prepare his or her own meals, the person who does the cooking receives the dietary advice as well.

Participants in the control group receive 20 minutes of coordinated advice for care and maintenance of dentures in the form of an explanation of a pamphlet prepared with reference to the guidelines published by the American Collage of Prosthodontics [23], after which the pamphlet is provided to the participant. The advice on diet and care and maintenance of dentures is provided by the two outcome assessors (HS and NA). The two-time deliveries of advice in the dietary intervention and control groups are designed to fit with dental appointments for try-insertion and delivery of new dentures.

### Outcome measures

Outcome measures are assessed at baseline and at 3 and 6 months following the intervention, with the exception of antioxidant capacity (Fig. 1). Antioxidant capacity data are collected at baseline and at 3 months following the intervention. The outcome assessments are to be done by three dentists (AJ, HS, and NA). The participants will be paid as a research corporation expenditure when outcome measure at 6 months following the intervention is completed. The outcome assessors will revise all completed questionnaires before the participants leave to avoid missing data at the end of each assessment. The recorded data are quickly deidentified and digitized, and will be stored and managed for ten years according to the rules of the institutional ethics committee of Tokyo Medical and Dental University.

**Fig. 1 Fig1:**
[figure not shown]
Chart of trial design

#### Primary outcome measures

The primary outcome measures are fruit, vegetable, and protein intake measured using a brief-type self-administered diet history questionnaire (BDHQ). The BDHQ enquires about the frequency of intake of 75 food items during the previous month. The daily intake of approximately 30 nutrients and about 50 food items is estimated. The validity and reliability of the BDHQ are established [24, 25].

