### Sample size estimation

The sample size was determined based on the two primary outcomes: changes in the weight of fruit and vegetable intakes and in the weight of protein intake. In case of change in the weight of fruit and vegetable intakes, 29 individuals per group would provide 80 % power to detect a difference of 125 g per day in intake, with a two-sided test at a 0.05 level of significance for the primary outcome. In case of change in the weight of protein intake, 30 individuals per group would provide 80 % power to detect a difference of 15 g per day in protein intake, with a two-sided test at a 0.05 level of significance for the primary outcome. We also anticipated a 15 % rate of loss to follow-up. Accordingly, we adjusted our target baseline sample size to 35 per group.

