### Statistical analysis

All analyses are to be based on the initial treatment assignment (intention to treat). Missing data will be replaced with multiple imputation to primary and secondary outcome variables. Differences between the groups at 3 and 6 months and within-group changes are to be compared using the paired *t* test. All statistical analyses will be performed using IBM Statistical Package for the Social Sciences (SPSS) Statistics version 17.0 software. A significance level of 0.05 is used for each test.

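### The primary outcomes are counted as three in one section and two in another, and are tested at 3 and 6 months at 0.05 each, with no primary time point and no rule for combining the tests

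*Protocol article*

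**What the plan says.** All references are to the protocol article.

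- **Primary outcome measures** names three intakes: "The primary outcome measures are fruit, vegetable, and protein intake measured using a brief-type self-administered diet history questionnaire (BDHQ").
- **Sample size estimation** counts differently: "The sample size was determined based on the two primary outcomes: changes in the weight of fruit and vegetable intakes", with protein weight as the second. For the first it states that "29 individuals per group would provide 80 % power to detect a difference of 125 g per day in intake". For protein it gives 30 per group for 15 g/day at the same power. Each calculation is made "with a two-sided test at a 0.05 level of significance for the primary outcome". After 15% loss to follow-up the target is 35 per group. No standard deviation and no time point are given.
- **Outcome measures** sets the schedule: "Outcome measures are assessed at baseline and at 3 and 6 months following the intervention, with the exception of antioxidant capacity".
- **Statistical analysis** uses both follow-up visits: "Differences between the groups at 3 and 6 months and within-group changes are to be compared using the paired" *t* test. It then fixes the error rule: "A significance level of 0.05 is used for each test".
- **Background** frames a single null hypothesis, about dietary intake as a whole.

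No section names a primary time point, orders the primary tests, adjusts for their number, or requires all of them to succeed.

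**The concern.** Two sections disagree on what the primary outcomes are. One lists fruit and vegetables as separate items; the other combines them into one quantity and powers only that. Fruit alone and vegetables alone have no power calculation.

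Crossed with two follow-up times, this gives four between-group primary tests on the sample size section's count and six on the outcome section's list. Each is run at 0.05, and each could be read as rejecting the one null hypothesis about dietary intake. At stake is what a positive result would mean. Depending on how the tests are combined, either the false-positive rate of the primary claim exceeds 5%, or the power of that claim is below the stated 80%.

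**Working it through.** **Inputs from the protocol article.** Two or three primary outcomes; two follow-up times; two-sided 0.05 per test; 80% power at 29 per group for 125 g/day and at 30 per group for 15 g/day; 15% loss; 35 per group enrolled; 1:1 allocation. **Assumed:** all correlations, since none is given. The power figures use a two-sample *t* test for the between-group comparison.

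**1. The plan's own figures.** Without a standard deviation, 29 and 30 cannot be reproduced independently. Solving the noncentral *t* for 80% power gives:
- fruit and vegetables: standardized difference 0.749, so SD = 125/0.749 ≈ 167 g/day;
- protein: standardized difference 0.736, so SD = 15/0.736 ≈ 20.4 g/day.

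For enrolment, 30 × 1.15 = 34.5, which rounds to the stated 35; 30/0.85 = 35.3 would round to 36. The difference is immaterial here. Expected completers are 35 × 0.85 = 29.75 per arm.

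**2. Family-wise error if any one significant test counts as success.** Under independence it is 1 − 0.95^k. Under correlation it was found by simulating multivariate normal test statistics (500,000 draws per setting).

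| Primary tests | Independent | Correlation 0.5 between outcomes, 0.5 between times | Correlation 0.7 between outcomes, 0.8 between times |
|---|---|---|---|
| 2 outcomes × 2 times (k = 4) | 1 − 0.95^4 = 18.5% | 16.2% | 12.8% |
| 3 outcomes × 2 times (k = 6) | 1 − 0.95^6 = 26.5% | 22.0% | 16.5% |

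**3. Power if both powered outcomes must succeed at one time point.** There is no inflation in this case. With 80% for each outcome, joint power is 0.80 × 0.80 = 64% if they are independent, 66.6% at correlation 0.3, 68.7% at 0.5 and 71.3% at 0.7. Using 29.75 completers per arm instead moves these by less than one percentage point, so the range is about 64–72%.

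**4. Power with two outcomes, one time point and Holm at overall 0.05.** With 29.75 completers per arm and the back-solved SDs:

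| Outcome | Alpha 0.05 | Alpha 0.025 (first Holm step) |
|---|---|---|
| Fruit and vegetables | 81.0% | 72.0% |
| Protein | 79.7% | 70.3% |

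Under Holm, an outcome is declared if it passes 0.025, or if it passes 0.05 and the other passes 0.025. With both effects present and independent outcomes:
- fruit and vegetables: 0.720 + (0.810 − 0.720) × 0.703 = 0.783;
- protein: 0.703 + (0.797 − 0.703) × 0.720 = 0.771.

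Simulation with outcome correlation up to 0.7 lowers these only to about 77% and 76%.

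**The case against.** The best defence is that this is a condensed article and the analysis plan is not shown. A hierarchy among endpoints often sits there, and 0.05 for each test is compatible with fixed-sequence testing, where every step also uses 0.05. This stands in part: the missing multiplicity rule is weaker ground than the conflict between the two sections. But a later plan could not simply fill a gap. It would have to choose between two stated definitions of the primary outcomes and qualify a flat error rule that the article states outright.

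A reader might also infer stronger points that the document does not support:

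- **That the trial has a false-positive rate of up to about 27%.** This needs six independent tests and a rule that any one suffices. The protocol states no such rule. Independence is also implausible for one questionnaire repeated in the same people three months apart.
- **That 80% power covers only one test.** The sample size section gives it separately for each of two outcomes, each taken alone at unadjusted 0.05.
- **That the headline result will be picked after the data are seen.** The shown text does not prevent this, but the full protocol and analysis plan are unseen, so it is not established.
- **That the roughly 30 nutrients and 50 food items from the questionnaire add to the problem.** Those other than the primary intakes are labelled secondary, and no confirmatory claim is attached to them.
- **That correcting for multiplicity costs the full drop to 70–72%.** Those are first-step values. Under full Holm with both effects present, the loss is smaller.

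**Conclusion.** The point holds. The two sections must be reconciled, and the primary analysis as written does not fix a single error rate or power for the trial's claim.

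Its size depends on a rule that the protocol does not state:
- **Any one test suffices:** family-wise error of about 13–18.5% on the sample size section's count of two outcomes, or 17–26.5% on the outcome section's list of three. The lower ends assume correlations of 0.7 between outcomes and 0.8 between times; the upper ends assume independence.
- **Both powered outcomes must succeed at one time point:** error is controlled, but joint power is about 64–72% for outcome correlations of 0 to 0.7.

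On either rule, the stated 80% describes each powered outcome taken alone in a single unadjusted comparison, not the trial-level claim. The Holm power figures also rest on SDs back-solved from the stated sample sizes.

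**What to change.** 1. Make the outcome section match the sample size section, with two primary outcomes: combined fruit-and-vegetable weight and protein weight.
2. Name one primary time point and make the other secondary. The investigators should choose it, before outcome data are seen by group. Nothing in the article settles whether it should be 3 or 6 months.
3. For the two primary outcomes, replace the flat 0.05 per test with Holm at overall 0.05.
4. Report fruit alone, vegetables alone and the other questionnaire items as secondary estimates with confidence intervals and no confirmatory claim.
5. State the standard deviations used and restate power: about 72% and 70% at the first Holm step, and about 77–78% and 76–77% per outcome under full Holm when both effects are present.

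The trial status section says recruitment is still under way, so the change costs only wording. The downside is a stated power slightly below 80%. If 80% were wanted at alpha 0.025 for each outcome, 36 and 37 evaluable participants per group would be needed. That is 36/0.85 = 42.4 and 37/0.85 = 43.5, so 43 and 44 enrolled, against the planned 35.

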#### Secondary outcome measures

##### Dietary intake

The daily intakes of nutrients and food items, except for the primary outcomes, are assessed using the BDHQ [24, 25].

##### Assessment of antioxidant capacity

Antioxidant capacity will be assessed at baseline and at 3 months following intervention. The antioxidant potential is determined using a blood sample, and 8-hydroxy-2′-deoxyguanosine, a marker of oxidative stress, is measured in a urine sample. These markers are sensitive to changes in dietary intake of fresh fruit and vegetables. A 5-mL blood sample from each participant is collected into a K2EDTA vacutainer, from which plasma is separated and stored at −73 °C prior to analysis. All participants are required to have fasted for more than 8 hours prior to sampling, and all blood samples are taken at noon. Participants are also required to provide a 3-mL sample of morning urine.

##### Nutritional status

Nutritional status is assessed with the Mini-Nutritional Assessment-Short Form (MNA-SF) [26]. The MNA-SF has the option of using calf circumference when body mass index is not available. A score between 8 and 11 indicates a risk of deficient nutrition, and scores lower than 7 indicate malnutrition.

##### Anthropometric measurements

Weight and body composition are assessed by bioelectrical impedance (Tanita Inner Scan BC-522; Tanita, Tokyo, Japan). Body composition is estimated by determining body fat percentage.

##### Oral health-related quality of life

Oral health-related quality of life is assessed using the Japanese versions of the Oral Health Impact Profile-EDENT [27] and the Geriatric Oral Health Assessment Index [28] questionnaires. The Japanese version of the Oral Health Impact Profile-EDENT contains 19 questions and seven conceptual subscales: functional limitation, pain, psychological discomfort, physical disability, psychological disability, social disability, and handicap. Higher scores indicate lower oral health-related quality of life. The Japanese version of the Geriatric Oral Health Assessment Index contains 12 questions and three conceptual fields: functional field, psychosocial field, and pain and discomfort field. Higher scores indicate better oral health-related quality of life.

